#### 2.7.3. Sham Acupuncture (SA) Group

Participants in the SA group will receive sham acupuncture treatment eight times twice a week for four weeks. Unlike the VA group, SA group patients will receive sham acupuncture treatment at only six fixed control points. These bilateral acupoints are as follows: 1 to 2 cm proximal and 1 cm medial to LI7, 1 cm proximal and 1 cm medial to LI11, and 1 cm proximal and 1 cm lateral to ST36. To maintain participant blinding, a nonpenetrating sham device (Park sham acupuncture needles, AcuPrime Co., Ltd., Exeter, UK) will be used and left in place for 15 minutes.

After removal of sham acupuncture needles, the IA procedure used in the VA group will be replaced with application of needle-free, stainless steel rings that do not penetrate the skin. These will be attached to three control points: 1 cm proximal and 1 cm medial to LI11 bilaterally and finger point in the ear contra-laterally to the side with more severe symptoms. Unlike the VA group, SA group patients will not be instructed to press the control point.

#### 2.7.4. After Treatment

Two weeks after the eighth visit for the final acupuncture treatment, a telephone interview will be conducted to assess the severity of AD and dyspepsia symptoms, side effects after acupuncture treatment, and whether or not other treatments were used during the trial. During a final visit, four weeks after the eighth visit, the participant will complete a final evaluation. No other treatments will be allowed during the study period.

### 2.8. Compliance and Discontinuation

Frequent hospital visits may be a burden to the participant, resulting in withdrawal from the study. Based on the results of our pilot study [19], we determined that completion of six to eight treatment sessions was sufficient for a participant to be considered compliant and yield acceptable data. For dropouts who do not fulfil this criterion, the last observed data will be used for the analysis. The research coordinator will keep in contact with participants to encourage them to continue participation to the end of the trial.

### 2.9. Outcome Measures

A researcher who is independent of this study will evaluate the outcomes. The schedule is shown in Table 2. The primary measurable outcome is the change in SCORAD (total) before treatment (baseline) and after (at four weeks) Treatment. Secondary outcomes are as follows: (1) baseline to four-week changes in AD symptoms, QoL, GI symptoms, or EEG and (2) changes between baseline and second, fourth, and eighth weeks in AD symptoms and QoL. Measurable values are as follows: SCORAD Index, Eczema Area and Severity Index (EASI), Patient Oriented Eczema Measure (POEM), Dermatology Life Quality Index (DLQI), abdominal Pressure Pain Threshold (PPT) using an algometer developed in the Korea Institute of Oriental Medicine [29], questionnaires about dyspepsia symptoms (Nepean Dyspepsia Index-Korean version, Adequate Relief of functional dyspepsia pain and discomfort, and VAS for dyspepsia), and EEG.

#### 2.9.1. Scoring Atopic Dermatitis (SCORAD)

SCORAD was developed in 1993 by the European Task Force on Atopic Dermatitis as a useful scoring system that assesses the severity of AD by its extent, intensity, and subjective symptoms [28, 30, 31]. The extent component of SCORAD is assessed using the rule of nines for AD lesions. The intensity component of SCORAD is divided into erythema, edema and papules, oozing and crust, excoriation, lichenification, and dryness. Subjective symptom measures are the degrees of pruritus and sleep disturbance assessed on the VAS.

#### 2.9.2. Eczema Area and Severity Index (EASI)

EASI is a tool for evaluating the severity of AD symptoms. Like the SCORAD index, it is known as a useful evaluation tool [30, 32, 33]. Body parts are divided into four parts (head and neck, trunk, upper limb, and lower limb) to evaluate the extent of AD lesions. The severity of symptoms (erythema, edema and papules, excoriation, and lichenification) is then evaluated.

#### 2.9.3. Patient Oriented Eczema Measure (POEM)

POEM is a simple, easily understood, and well-validated tool for evaluating the severity of AD symptoms in the preceding week. It is known to be appropriate for use in outpatient clinic or clinical trial settings [30, 34].

#### 2.9.4. Dermatology Life Quality Index (DLQI)

DLQI is a well-validated clinical research tool that is widely used to assess the QoL of patients with dermatologic symptoms. It evaluates the effect of skin disease on QoL during the preceding week and consists of 10 questions [35, 36].

#### 2.9.5. Abdominal Examination Using Pain Pressure Threshold (PPT)

In Korean Medicine, KMDs use abdominal examination for diagnosis, choice of treatment methods, and/or evaluation of prognosis [37]. We will standardize and describe abdominal examination quantitatively using the PPT algometer. The PPT algometer used in our pilot study [19] was found to be unsuitable for abdominal examination, so a more appropriate algometer developed in the Korea Institute of Oriental Medicine will be used [29]. The outcome assessor will apply the algometer before and after acupuncture treatment to measure the patient's abdominal tenderness at four acupuncture points (CV17, CV12, and bilateral ST25). Pressure at each acupoint will be delivered at a constant force and velocity following the computerized guide. Each measurement will be performed three times for 1 minute [38].

#### 2.9.6. Nepean Dyspepsia Index (NDI)

NDI is a reliable scale for functional dyspepsia which evaluates dyspepsia symptoms and related QoL. NDI consists of period, severity, and degree of distress of 15 dyspepsia-related symptoms [39, 40]. In this study, participant will be asked to answer the Korean version of NDI (NDI-K) [41].

#### 2.9.7. Adequate Relief of Functional Dyspepsia Pain and Discomfort (AR)

AR assesses improvement in overall functional dyspepsia symptoms [42]. Subjects will be asked to answer the following question: “Have you experienced appropriate relief (more than 50% reduction) of the pain or discomfort associated with your dyspepsia after the last acupuncture treatment?”

#### 2.9.8. VAS for Functional Dyspepsia

Using 100 mm VAS (0 mm for no discomfort to 100 mm for the worst discomfort), we will measure a degree of overall dyspeptic symptoms.

#### 2.9.9. Credibility/Blinding Test

In order to evaluate the credibility of the study participants' acupuncture treatment, a questionnaire-type credibility test will be conducted at the first and eighth treatment visits and the follow-up visit [43]. The following question will also be asked once at the eighth treatment visit when the last treatment is given: “Which group do you think you belonged to? The treatment group or the control group, and why?” This question aims to determine the direction and degree of blinding between the VA group and the SA group [44].

#### 2.9.10. Measurement of Electroencephalography (EEG)

Subjective feelings of itchiness in AD may be induced or enhanced by watching someone scratch himself or herself. Brain signals associated with somatosensory perception may be changed by contagious itch [45]. Visual stimuli depicting scratching behavior can induce changes in oscillatory potentials measured with EEG. This study is designed to explore the relationship between neuronal oscillations and subjective itchiness induced by contagious itch.

All patients will be asked to evaluate how much itchiness they feel after watching video clips of a person either scratching or performing a control movement. Their evaluation will use a visual analog scale ranging from 0 to 10. Continuous EEG will be recorded using Brain Products EEG amplifiers with a 32-channel ActiCAP system according to the international 10-20 system. Event-related spectral perturbation (ERSP) methods will be applied to EEG data, while patients are watching the video clips. Through time-frequency analysis, the suppression of mu activity will be measured over central-parietal regions. Mu rhythm represents frequencies in the range of 8-13 Hz, and the suppression of mu activity can be observed over the primary sensorimotor cortex when an action is performed, observed, or imagined [46]. The EEG results will be compared within each patient between scratching and control movement videos. We hypothesize that the suppression of mu activity over the sensorimotor cortex will be decreased after the treatment in the VA group but not in the SA group.

### 2.10. Sample Size Calculation

Sample size calculation was carried out using G*∗*Power 3.1.9.2 for Windows 10. The primary measurable outcome in this study is the change in SCORAD (total) before treatment (at baseline) and at the end of treatment (four weeks). We derived the sample size of this study using information from our pilot study [19] showing a change in total SCORAD at baseline and after treatment of 13.0 ± 9.9 and 4.6 ± 5.0 in the VA and SA groups, respectively, and effect size d was 1.1. Based on this, the critical t-value was 2.0 for 28 degrees of freedom, and the noncentrality parameter *δ* was 3.0 (two-tailed independent* t*-test) at 5% significance level, with 80% power and 20% dropout rate. Required sample size was calculated as 18 per group.

### 2.11. Statistical Analysis

Statistical analyses will be performed by an independent statistician who is unaware of group assignments, using IBM SPSS for Windows (Version 21.0). Continuous variables will be presented as mean ± 1 standard deviation, and bivariate variables will be presented as numbers (%). The effect of the intervention will be assessed as the change in outcome measures between baseline and four weeks (after treatment sessions end) and through eight weeks (after follow-up period ends), using a repeated-measures analysis of variance (ANOVA) and *χ*2 test. The difference in effect between VA and SA will be assessed by comparing changes in the SCORAD (total) index, the AD symptoms, QoL, dyspepsia symptoms, and EEG outcomes, using the independent* t*-test or Mann–Whitney *U* test on continuous variables and *χ*2 test or Fisher's exact test on categorical variables.

ITT (intention-to-treat) analysis will be used for all participants who have undergone at least one acupuncture treatment. For missing values, the last observation carried forward (LOCF) method will be applied. PP (per protocol) analysis will be used for only the participants who have completed the entire course of the test exactly as specified in the trial plan. Primary evaluation of the intervention effect will be based on the results of the ITT analysis.

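### Section 2.11 labels a change over time as the intervention effect and does not name the VA-SA difference as the primary contrast

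*Protocol article*

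**What the plan says.** Section 2.11 (Statistical Analysis) of the protocol article sets out two analyses, one after the other.

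- **Change over time.** "The effect of the intervention will be assessed as the change in outcome measures between baseline and four weeks", and on through the end of follow-up at week 8, "using a repeated-measures analysis of variance (ANOVA) and" a χ² test. Neither an arm term nor an arm-by-visit term is named.
- **Between arms.** "The difference in effect between VA and SA will be assessed by comparing changes in the SCORAD (total) index", together with the AD symptom, QoL, dyspepsia and EEG outcomes, by independent t-test or Mann–Whitney U test (χ² or Fisher's exact test for categorical variables).

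The section closes with "Primary evaluation of the intervention effect will be based on the results of the ITT analysis". That sentence fixes the analysis set and reuses the term from the first analysis, but names no contrast.

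Section 2.9 words the endpoint in the same before-after way: "The primary measurable outcome is the change in SCORAD (total) before treatment (baseline) and after (at four weeks) Treatment". The main objective in section 2.1 speaks of improvement and does not mention sham.

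Section 2.10 rests on the between-arm contrast. It uses a two-tailed independent t-test on pilot changes in total SCORAD of "13.0 ± 9.9 and 4.6 ± 5.0 in the VA and SA groups". Section 2.9.10 words the EEG hypothesis by arm: mu suppression "will be decreased after the treatment in the VA group but not in the SA group".

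**The concern.** Only the VA-SA comparison is protected by randomisation. A change from baseline within an arm, or averaged over both arms, also contains everything else that moves the score: natural course, expectation, regression to the mean after entry on minimum itch and objective SCORAD scores, the preceding month without prescribed AD medication (section 2.3.1), and the lifestyle advice given to all participants (Table 1, item 4a).

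The between-arm difference has its own sentence and its own tests, so the natural reading of the sentence before it is change over time. The plan gives that quantity the name that its primary evaluation then uses. An analyst could follow section 2.11 as written, find a significant change from baseline, and report it as the intervention effect even though the VA-SA test showed nothing.

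**Working it through.** **Inputs.** Pilot change in total SCORAD: VA 13.0 (SD 9.9), SA 4.6 (SD 5.0). Two-sided 5% level, 80% power, 20% dropout, 28 degrees of freedom, 18 per group. All are from section 2.10.

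**1. Which contrast was the trial sized for?**
- Pooled SD = √((9.9² + 5.0²)/2) = √61.505 = 7.84.
- d = (13.0 − 4.6)/7.84 = 1.07 (stated as 1.1).
- With 15 per group: df = 28, critical t = 2.048, noncentrality = 1.07 × √(15/2) = 2.93 (3.01 with d = 1.1), power 80.8% (82.8%).
- 15 × 1.2 = 18 per group, the stated figure. Dividing by 0.8 gives 18.75, that is 19.

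The stated sample size therefore reproduces as a VA-versus-SA comparison of changes.

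**2. How often would sham alone show a significant change?**
- Standardised change = 4.6/5.0 = 0.92.
- Noncentrality of the one-sample t-test = 0.92 × √n: 3.56 for n = 15 and 3.90 for n = 18.
- Power from the noncentral t distribution: 91.1% (n = 15) and 95.7% (n = 18).
- If 18 patients showed exactly the pilot figures: t = 4.6/(5.0/√18) = 3.90, df 17, p = 0.0011.

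**3. What if VA were no better than sham?** Both arms are assumed normal with mean change 4.6 and SD 5.0. The first two rows are noncentral-t results; the last two come from 40,000 simulated trials per setting.

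| Result at two-sided 5% | 15 per arm | 18 per arm |
|---|---|---|
| Change within VA significant | 91% | 96% |
| Change pooled over both arms significant | 99.8% | over 99.9% |
| VA-SA test significant | 4.9% | 5.0% |
| Change within VA significant, VA-SA test not | 87% | 92% |

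**4. Less favourable assumption.** Suppose VA had the sham mean of 4.6 but the pilot VA SD of 9.9, a standardised change of 4.6/9.9 = 0.46. The within-VA test would then be significant 39% (n = 15) to 46% (n = 18) of the time. That is still far above 5%.

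**The case against.** The strongest reply is that the controlled comparison is already there. It is the next sentence of section 2.11 and lists total SCORAD first. It determines the sample size in section 2.10. The Discussion (section 3) also justifies the treatment frequency by its ability to show effects between VA and SA. The first sentence never says that the analysis is within arm, and the repeated-measures ANOVA may be meant to include arm: the Discussion describes pilot results as differing between groups over time. All of this stands, and it limits the point to wording and priority. It does not remove the point, because no sentence says which analysis answers the primary question, and the term used for the primary evaluation is the one attached to change over time.

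The regression-to-the-mean argument is also weaker than the lower entry limits alone suggest. Section 2.3.1 sets upper limits too, and section 2.3.2 excludes severely fluctuating disease. The calculation does not need that argument, since the pilot sham arm improved whatever the reason.

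A reader might infer from section 2.9.10 that an EEG effect could be claimed without any arm difference, because a change in VA and none in SA is a difference in significance. The documents do not support that. Section 2.11 lists EEG among the outcomes compared between arms, and no separate within-arm EEG tests are planned. What remains is a mismatch between the worded hypothesis and the planned test.

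**Conclusion.** The point holds as one of definition and priority. Section 2.11 attaches the name of the intervention effect to an analysis with no stated arm contrast, and the primary evaluation inherits that name. On the protocol's own pilot figures, a within-arm test would be significant in sham about 91% to 96% of the time. This assumes that the pilot sham mean and SD carry over and that 15 to 18 patients per arm contribute. It describes what the wording permits and does not predict what will be reported.

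Two stronger readings should be resisted. The first is that the trial lacks a controlled primary test; sections 2.10 and 2.11 show otherwise. The second is that the repeated-measures ANOVA has an inflated false-positive rate because no sphericity correction is named. Such a correction is a detail commonly left to the analysis plan. The concern also presupposes an arm-by-visit test, which the text does not state. At the visits that section 2.9 names (baseline and weeks 2, 4 and 8), simulated error was only about 5% to 7%, under an assumed correlation.

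**What to change.** Reword section 2.11 along these lines:

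> *The effect of the intervention is the VA-SA difference in change in total SCORAD from baseline to week 4. Its primary evaluation is this contrast in the ITT set, adjusted for baseline total SCORAD. Repeated-measures analyses will be interpreted through the arm-by-visit contrast. Changes within each arm will be described without p-values.*

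The adjustment can be an ANCOVA or the equivalent contrast from a mixed model. Baseline SCORAD is already collected (Table 2). Adjustment is a preference: if the sponsor keeps the independent t-test on changes as the primary test, naming it as such still cures the fault described here.

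For consistency, state the EEG hypothesis in section 2.9.10 as a between-arm difference in the change in mu suppression, which section 2.11 already plans to test.

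The cost is a few sentences and the loss of within-arm p-values. If the adjusted analysis is chosen, it replaces the t-test or Mann–Whitney test as the primary method. No new data are needed, and the sample size of 18 per group stays, because it was calculated for this contrast.

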	(i) A control group (SA) will be treated with sham acupuncture using Park sham acupuncture needles and nonpenetrating sham PTNs
	(6b) Precise description of the control or comparator. If sham acupuncture or any other type of acupuncture-like control is used, provide details as for items (1) to (3) above
	MA: Park sham acupuncture needles and devices will be used in same environment as in the VA group. However, fixed acupoints will be different: a point 1 to 2 cm proximal and 1 cm medial to LI7, a point 1 cm proximal and 1 cm medial to LI11, and a point 1 cm proximal and 1 cm lateral to ST36, each bilaterally
	IA: Nonpenetrating sham PTNs, which were designed and validated for blinding for our study, will be used as a control in same environment as in the VA group. The same sized stainless steel rings without needles will be attached to three control points: a point 1 cm proximal and 1 cm medial to LI11, bilaterally, and finger point in the ear contralaterally.

**Table 2 tab2:** *Study Schedule*. VAS: Visual Analog Scale; SCORAD: Scoring Atopic Dermatitis; EASI: Eczema Area and Severity Index; POEM: Patient Oriented Eczema Measure; DLQI: Dermatology Life Quality Index; PPT: Pain Pressure Threshold; NDI-K: Nepean Dyspepsia Index-Korean version; AR: Adequate Relief of functional dyspepsia pain and discomfort; EEG: Electroencephalography. ● represents treatment applied at that particular interval; 

: participant contacted by telephone.

Treatment and measure	Baseline	Treatment period				Follow-up period			
		1 week	2 weeks	3 weeks	4 weeks	5 weeks	6 weeks	7 weeks	8 weeks
Demographics	●								

Physical Examination	●								

Medical history	●								

VAS for itch	●	●	●	●	●				●

VAS for sleep loss	●	●	●	●	●				●

VAS for dyspepsia	●	●	●	●	●				●

SCORAD assessment	●	●	●	●	●				●

EASI assessment		●	●	●	●				●

POEM assessment		●	●	●	●				●

DLQI assessment		●	●	●	●				●

PPT evaluation		●	●		●				

NDI-K assessment		●			●				●

AR assessment				●	●				●

Credibility test		●			●				

Blinding test					●				

EEG assessment		●			●				

Acupuncture Treatment		●	●	●	●				

Adverse Events		●	●	●	●				●

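### LOCF is the only stated rule for missing SCORAD values at weeks 4 and 8, so the treatment contrast depends on when, and from which arm, patients leave

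*Protocol article*

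**What the plan says.** The general rule in section 2.11 is "For missing values, the last observation carried forward (LOCF) method will be applied". Section 2.8 adds a rule for participants who stop before completing six sessions: "For dropouts who do not fulfil this criterion, the last observed data will be used for the analysis".

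These rules reach the main result. Section 2.11 states "Primary evaluation of the intervention effect will be based on the results of the ITT analysis", and defines the set as follows: "ITT (intention-to-treat) analysis will be used for all participants who have undergone at least one acupuncture treatment". Someone who leaves after one session is therefore in the primary analysis and must be given a week-4 value. The primary endpoint in section 2.9 is the change in total SCORAD from baseline to week 4. Among the secondary outcomes are "changes between baseline and second, fourth, and eighth weeks in AD symptoms and QoL", and section 2.11 takes the repeated-measures ANOVA through week 8.

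Table 2 marks the row "SCORAD assessment" at baseline and at weeks 1, 2, 3, 4 and 8. Section 2.10 plans for 20% dropout. The only other analysis stated is per protocol, which leaves out the participants whose data are incomplete. The article states no missing-data sensitivity analysis.

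**The concern.** LOCF treats the last recorded score as the score at every later visit. That is right on average only in special cases, such as no further change after the last visit. The plan's own assumptions point the other way: over four weeks it expects mean improvements of 13.0 points on VA and 4.6 on SA. Freezing an early leaver therefore removes more improvement from a VA patient than from an SA patient, and the net effect depends on how many leave each arm and when.

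Week 8 raises a separate problem. Treatment ends at week 4, and the follow-up visit asks whether the benefit lasts. Carrying an on-treatment value forward assumes the persistence that the visit is meant to test.

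A filled-in value is also analysed as if it had been observed, which can misstate the standard error. The size and direction of that effect were not calculated. What is at stake is the size, and in some patterns the existence, of the reported contrast.

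**Working it through.** **Inputs.** From section 2.10: changes of 13.0 (SD 9.9) on VA and 4.6 (SD 5.0) on SA, two-sided 5% level, 80% power, 28 degrees of freedom, 20% dropout, 18 per group. The article does not give the timing of dropout, its split by arm or the course of change, so these are assumed below.

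**The plan's own figure.** The contrast is 13.0 − 4.6 = 8.4. The SD is √((9.9² + 5.0²)/2) = 7.84, so d = 8.4/7.84 = 1.07, given as 1.1. With 15 per group (28 df), power is 80.8% at d = 1.071 and 82.8% at 1.1. Then 15 × 1.2 = 18, so the stated size reproduces.

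**Week 4 under LOCF.** Let p be the share of an arm that drops out and f the fraction of the week-4 change reached at the last visit. The expected arm mean is m × (1 − p(1 − f)). With linear change and last visits spread evenly over weeks 0, 1, 2 and 3, f = (0 + 0.25 + 0.5 + 0.75)/4 = 0.375.

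| Dropout VA / SA | VA mean | SA mean | Contrast (true 8.4) |
|---|---|---|---|
| 20% / 20% | 13.0 × 0.875 = 11.375 | 4.6 × 0.875 = 4.025 | 7.35 (−12.5%) |
| 30% / 10% | 13.0 × 0.8125 = 10.5625 | 4.6 × 0.9375 = 4.3125 | 6.25 (−25.6%) |
| 10% / 30% | 13.0 × 0.9375 = 12.1875 | 4.6 × 0.8125 = 3.7375 | 8.45 (+0.6%) |

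For equal 20% dropout, the contrast is 6.72, 7.14, 7.56 or 7.98 if every last value is at baseline, week 1, 2 or 3. With 5% VA and 30% SA it ranges from 9.13 (baseline) to 8.58 (week 3), an inflation.

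**Power.** With all 18 per group analysed and SD 7.84, power is 87.7% at 8.4 points and 78.0% at 7.35. This ignores any effect of LOCF on the SD.

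**No true difference.** Let both arms improve by 8.8 points, the mid-point of 13.0 and 4.6. With 30% VA and 10% SA dropout and f = 0.375, LOCF gives 8.8 × (0.8125 − 0.9375) = −1.10. Reversing the split gives +1.10.

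**Simulation.** This used 400,000 patients per arm, weekly visits and a value at week 1 for everyone. Dropout was more likely after a poor last observed response, and 60% of the week-4 variance was between patients. LOCF was compared with a likelihood-type estimate (sequential normal regression within arm).

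| True contrast | Dropout VA / SA | LOCF | Likelihood-type |
|---|---|---|---|
| 8.4 | 20% / 20% | 7.40 | 8.42 |
| 8.4 | 34% / 6% | 5.72 | 8.40 |
| 8.4 | 6% / 34% | 8.99 | 8.39 |
| 0 | 34% / 6% | −1.78 | 0.01 |
| 0 | 6% / 34% | +1.48 | 0.02 |

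Dropout here depends only on observed values, so the good result for the likelihood-type estimate is expected. It does not show protection against other mechanisms.

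**Week 8, benefit fully faded (true contrast 0), 20% lost in each arm.** If all leave after week 4, LOCF shows 0.2 × 8.4 = 1.68. If they leave over weeks 0 to 3 as above, it shows 0.2 × 0.375 × 8.4 = 0.63. If the effect is fully kept to week 8, carrying week 4 forward causes no bias.

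**The case against.** The strongest reply is that LOCF may do little harm here, or harm only the sponsor's own hypothesis. The article gives one overall dropout figure. With equal dropout the week-4 contrast shrinks towards zero, and 78.0% power at 7.35 points is not far below the 80.8% planned with 15 per group. The 6.25 figure needs a 30%/10% split that the documents do not suggest. Retention contact by the coordinator and frequent SCORAD visits limit how much is carried forward, and how far. All of this stands. It makes the size uncertain but does not make LOCF sound, because nothing in the plan secures equal dropout.

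A reader might also infer that patients leave when they flare and that a mixed model would correct for it. The documents do not support the first step: exclusion criterion (A) in section 2.3.2 removes severely fluctuating disease, and no flare-driven dropout is described. The second step fails as well. If the flare is never recorded, the data are missing not at random, and a mixed model uses the same pre-flare values. The case against LOCF needs only change after dropout.

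There are practical objections to a replacement model too. Section 2.9 names weeks 2, 4 and 8, while Table 2 marks every treatment week. The week-1 column appears to include the first treatment visit: the credibility test that section 2.9.9 places at that visit is marked there, and EASI, POEM and DLQI have no earlier mark. Week-1 SCORAD may therefore precede treatment. A patient with no post-baseline value is lost from a model that uses baseline only as a covariate, and a large unstructured covariance is heavy for 36 patients. These points stand and shape the fix.

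**Conclusion.** The concern holds as a weakness in a stated choice for the primary analysis. Under the planning means, linear change and last visits spread over weeks 0 to 3, equal 20% dropout takes about 1 point (12.5%) off the week-4 contrast. Unequal dropout moves it in either direction and can produce a contrast of a point or more from nothing. At week 8, with full loss of benefit, the overstatement is about 0.6 to 1.7 points. The upper end requires every dropout to occur after week 4.

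A reader might infer that LOCF necessarily favours VA, or that it is safely conservative. The documents support neither reading. Direction depends on timing and arm, which the article does not give. At week 4, equal dropout works against VA; at week 8, a fading effect works in its favour. The change should be made, but the trial remains interpretable without it.

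**What to change.** Make the primary analysis a REML mixed model for repeated measures on total SCORAD:

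- **Visits.** Use weeks 2, 4 and 8 as in section 2.9. Add weeks 3 and 1 only where the Table 2 visit is confirmed to fall after treatment has started.
- **Terms.** Include group, visit and group-by-visit. Put baseline in the outcome vector with a common baseline mean, so that every treated patient contributes, including those with no later value.
- **Covariance.** Start with unstructured and name a simpler structure in advance in case it fails. Baseline plus three visits needs 4 × 5/2 = 10 parameters; baseline plus five visits needs 6 × 7/2 = 21, from 36 patients. Use a small-sample degrees-of-freedom method that the software offers.
- **Contrasts.** Week 4 is primary. Week 8 is secondary, from the same model.
- **Data collection.** Continue scheduled SCORAD assessments after treatment is stopped, where the patient agrees.
- **Sensitivity.** Add a missing-not-at-random analysis, for example delta-adjusted. Keep LOCF only as supplementary, and delete it as the primary method in sections 2.8 and 2.11.

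The cost is mainly wording in those two sections, clarification of the week-1 visit, and some follow-up of patients who stop treatment. The downside is reliance on missing-at-random in the primary analysis and somewhat more model specification.
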